## Abstract

**Background:**

Consistent and compelling evidence demonstrates that social and economic adversity has an impact on health outcomes. In response, many health care professional organizations recommend screening patients for experiences of social and economic adversity or *social risks*—for example, food, housing, and transportation insecurity—in the context of care. Guidance on how health care providers can act on documented social risk data to improve health outcomes is nascent. A strategy recommended by the National Academy of Medicine involves using social risk data to adapt care plans in ways that accommodate patients’ social risks.

**Objective:**

This study’s aims are to develop electronic health record (EHR)–based clinical decision support (CDS) tools that suggest social risk–informed care plan adaptations for patients with diabetes or hypertension, assess tool adoption and its impact on selected clinical quality measures in community health centers, and examine perceptions of tool usability and impact on care quality.

**Methods:**

A systematic scoping review and several stakeholder activities will be conducted to inform development of the CDS tools. The tools will be pilot-tested to obtain user input, and their content and form will be revised based on this input. A randomized quasi-experimental design will then be used to assess the impact of the revised tools. Eligible clinics will be randomized to a control group or potential intervention group; clinics will be recruited from the potential intervention group in random order until 6 are enrolled in the study. Intervention clinics will have access to the CDS tools in their EHR, will receive minimal implementation support, and will be followed for 18 months to evaluate tool adoption and the impact of tool use on patient blood pressure and glucose control.

**Results:**

This study was funded in January 2020 by the National Institute on Minority Health and Health Disparities of the National Institutes of Health. Formative activities will take place from April 2020 to July 2021, the CDS tools will be developed between May 2021 and November 2022, the pilot study will be conducted from August 2021 to July 2022, and the main trial will occur from December 2022 to May 2024. Study data will be analyzed, and the results will be disseminated in 2024.

**Conclusions:**

Patients’ social risk information must be presented to care teams in a way that facilitates social risk–informed care. To our knowledge, this study is the first to develop and test EHR-embedded CDS tools designed to support the provision of social risk–informed care. The study results will add a needed understanding of how to use social risk data to improve health outcomes and reduce disparities.

**International Registered Report Identifier (IRRID):**

PRR1-10.2196/31733

## Introduction

### Background

The conditions in which people live, work, and play—known as social determinants of health (SDH)—have well-documented impacts on health care access and quality and also on health outcomes [1-3]. SDH are shaped by broader social, economic, and structural forces and contribute to long-standing, avoidable health disparities and inequities [2]. Given the growing recognition of the impact of SDH on health, many health and health care professional organizations (eg, the American College of Physicians and the National Academy of Medicine) now recommend systematically screening for and documenting patients’ experiences of social adversity, including social risk factors related to food, transportation, and housing insecurity, in electronic health records (EHRs) [4-8]. As social risk data become more available in EHRs, it is important to understand how care teams can use this information to improve patient outcomes, which might reduce related health inequities.

A 2019 National Academies of Sciences, Engineering, and Medicine [9] report on integrating social and medical care describes a range of uses for reported social risk data in clinical settings. One such use is to provide or link patients with reported social risks to relevant social services, such as providing food resources to food-insecure patients or otherwise targeting social risks within the context of care delivery (*social risk–targeted care*). The National Academies of Sciences, Engineering, and Medicine report also describes a category of interventions that use social risk data to adapt care plans to account for a given patient’s social risks (*social risk–informed care*) [10]. Research on *social risk–targeted care* suggests that linking patients with social needs to specific social services can improve health outcomes [10-13]. Far less is known about the adoption and impact of social risk–informed care, although such care plan adaptations might improve health for individual patients and contribute to reducing disparities in care outcomes. For example, a social risk–informed care plan adaptation for a patient experiencing homelessness might involve avoiding refrigerated medications; for a patient with diabetes and food insecurity, it might include modifying insulin doses based on monthly food benefit schedules [14,15]. A series of studies in the Veterans Health Administration system found higher rates of positive clinical outcomes associated with social risk–informed care plan adaptations [16-20]. However, care that incorporates information about patients’ social context is not systematically incorporated into chronic disease management. Previous research found that social risk–informed care occurs only 15%-22% of the time in diverse care settings [21,22].

Social risk information must be presented to care teams in a manner that is useful to them and does not disrupt clinical workflows to encourage the systematic delivery of contextualized, social risk–informed care. Numerous studies have shown that clinical decision support (CDS) tools embedded in EHR systems can enhance care quality by providing clinical information to care teams along with suggestions on evidence-based actions relevant to a given patient’s care [23-29]. Such tools can include reminders about overdue screenings, summaries of a given patient’s health risks, and care recommendations per current guidelines. However, to our knowledge, the use and impact of EHR-based CDS to support the provision of contextualized, social risk–informed care has not been assessed.

### Objectives

This paper describes the protocol for a National Institutes of Health (NIH)-funded study (COHERE; Contextualized Care in Community Health Centers’ Electronic Health Records; R01MD014886) designed to develop and test CDS tools that present care team members with a given patient’s social risk information and both recommend and facilitate care plan adaptations based on those risks. This study will test the hypothesis that providing CDS that alerts care team members to patients’ known social risks and recommends relevant care plan adaptations will result in improved health outcomes. This study’s focus is on hypertension and diabetes control; however, the results will have implications for a wide range of morbidities.

## Methods

### Setting

The study will be conducted among community health centers (CHCs) that are members of OCHIN (not an acronym). OCHIN is a nonprofit health center–controlled network that hosts a single Epic EHR for >600 primary care CHCs located across the United States. As part of previous NIH-funded studies (1R18DK105463 and 1R18DK114701) and OCHIN’s ongoing CHC-centric EHR modifications, a suite of EHR tools was designed to enable documentation of social risk data and the provision of related referrals [23,30-33]. These tools were activated OCHIN-wide in June 2016; as of April 2021, >700,000 social risk screening results in >400,000 unique patients have been documented using these tools. The tools were adapted as their implementation was based on user input and to ensure alignment with the Epic EHR’s 2018 social determinants module. At present, the tools enable users to flag targeted patients for social risk screening, select from several screening tools (Protocol for Responding to and Assessing Patients’ Assets, Risks, and Experiences; the Centers for Medicaid/Medicare Services’ Accountable Health Communities screening tool; social risk questions from the Institute of Medicine [now the National Academy of Medicine]; or individual social risk domains) [34-37], enter patient-reported social risk data via several interfaces, and allow patients to self-enter data through the patient portal or at the point of care. The tools can also be used to document patients’ priorities related to social needs and interest in related referrals. In the trial described here, the CDS tools to be developed and tested will draw information on patient-reported social risks from data documented through these existing tools.

### Conceptual Guide

The conceptual framework proposed by DeVoe et al [38] for integrating SDH into primary care practice will guide the design of this intervention. A modified version of this framework (Figure 1) shows that data on self-reported social risks can be used to affect health care quality and outcomes either through panel management (eg, focused outreach) or at the point of care of individual patients through social risk–targeted care and social risk–informed care. This study focuses on EHR tools designed to facilitate point-of-care applications for social risk data, which have been proposed in theory but never formally tested.

**Figure 1 figure1:**
[figure not shown]
Social risk data and targeted or informed care (adapted from DeVoe et al [38]).

### Study Design

A randomized quasi-experimental design will be used to assess the impact of the newly developed CDS tools designed to support social risk–informed care. Before beginning the main trial, several formative activities and a pilot study will be conducted.

#### Formative Phase

First, potential care plan adaptations will be drawn from a systematic scoping review of social risk–informed care recommendations included in national hypertension and diabetes guidelines and our team’s prior research. Second, diverse CHC staff and patients will be asked to review and prioritize potential care adaptations. CHC staff will be invited to provide input through a stakeholder committee, whereas patients will be engaged using OCHIN’s established patient engagement panel. This process will help the research team determine (1) which social risks the study’s CDS tools will include, (2) the specific content of the CDS tools, and (3) the preferred form in which the CDS tools should appear in the EHR. The tools will then be pilot-tested for 12 months in three CHCs and further refined based on extensive user feedback from these pilot sites. Figure 2 outlines our process for developing the tools in preparation for the main trial.

**Figure 2 figure2:**
[figure not shown]
Steps involved in developing the clinical decision support tools. CDS: clinical decision support; CHC: community health center; EHR: electronic health record; NASEM: National Academies of Sciences, Engineering, and Medicine; SDH: social determinants of health [39,40].

#### Main Trial

Intervention clinics will have the CDS tools turned on in their EHR and will be followed for 18 months to assess (1) tool adoption, (2) the extent to which tool suggestions are enacted by care team members, and (3) the impact of tool use on two national clinical quality measures (CQMs) [41]: blood pressure control and hemoglobin A_1c_ (HbA_1c_) control. We will also assess care team members’ perceptions of the tools’ usability and impacts on care quality and patient-provider interactions.

### Randomization and Recruitment

All OCHIN clinics that provide primary care and have documented ≥200 social risk screenings (excluding the pilot clinics) will be identified. It is anticipated that approximately 60 clinics will meet these criteria. Eligible clinics will be randomized 1:1 to 1 of 2 groups: potential intervention or control. Clinics from the potential intervention group (n=30) will be recruited in random order until 6 agree to participate. In the study analyses, outcomes in these 6 intervention clinics will be compared with those in the control clinics (n=30). This approach allows for randomization between the intervention and control arms while eliminating the recruitment of CHCs to a study where some will receive no intervention (ie, only clinics that will receive the intervention will be contacted for recruitment). This method is possible as all OCHIN member CHCs agree that their EHR data may be used in research as part of their membership agreement.

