In secondary analyses, a repeated cross-sectional design will be used to assess the differential changes in the outcomes across time. A panel design is impractical in this population of CHC patients, so using repeated measures would result in a selective (eg, patients with stable and continuous care) and smaller sample. As we will be able to collect up to 18 months of data, we will subset the relevant patient subpopulations within clinics in 6-month increments and model time as a between-subjects effect in the model described above to evaluate the effectiveness for each outcome. More specifically, we will add time (6, 12, and 18 months) and the product of time and arm that represents their interaction in level 2 of the model. We will then calculate the population-averaged marginal proportions and associated 95% CIs by arm and time points, along with the marginal effects between arms within time points and between arms across pairs of time points (ie, differences-in-differences). Significant marginal effects between arms across time would suggest a differential change between the arms across time. As all secondary CQM outcomes (Textbox 1) are also binary, we will use the same approach to evaluate between-arm differences on these outcomes as for the primary outcomes.

Intent-to-treat analyses will be used to establish effectiveness at the population level and per-protocol analyses to assess the impact of the tools when used. For the primary analysis, depending on the size of the intraclass correlation (between 0.01 to 0.05), this study has at least 80% power to detect a 9%-17% difference in blood pressure control (n=343 per CHC; assuming baseline level of 60% blood pressure control calculated from OCHIN data) and a 10%-18% difference in HbA_1c_ control (n=214 per CHC; assuming baseline level of 34% HbA_1c_ control calculated from OCHIN data) between the intervention and control groups at a two-tailed α level of .05.

Primary and secondary analysis variables.

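### Clinics that decline after randomization drop out of the intervention arm only, so the 6 v 30 comparison is neither protected by randomization nor intent-to-treat as the protocol describes it

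*Protocol article*

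**What the plan says.** Under Randomization and Recruitment, the protocol article expects about 60 eligible clinics and allocates them at clinic level: "Eligible clinics will be randomized 1:1 to 1 of 2 groups: potential intervention or control". The intervention arm is then formed by consent: "Clinics from the potential intervention group (n=30) will be recruited in random order until 6 agree to participate". The stated analysis compares those 6 clinics with the 30 controls. Controls are not approached, because "only clinics that will receive the intervention will be contacted for recruitment". The same section says of the scheme: "This approach allows for randomization between the intervention and control arms".

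Under Quantitative Analyses the article adds: "Intent-to-treat analyses will be used to establish effectiveness at the population level". Per-protocol analyses are to assess the tools when they are used. Study Design uses a more guarded label: "A randomized quasi-experimental design will be used to assess the impact of the newly developed CDS tools". Limitations and Considerations does not mention clinics selecting themselves into the study.

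**The concern.** Random allocation makes the two groups of 30 comparable. Consent is then applied after allocation, to one group only. The intervention arm holds only clinics that said yes; the control arm still holds clinics that would have said no, and nobody knows which they are. If willingness to adopt a decision-support tool goes with staffing, quality-improvement activity or an existing trend in blood pressure or HbA1c control, that difference is confounded with the tools.

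The analysis as described does not remove it:

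- At clinic level the primary model has arm and a random intercept only.
- The candidate covariates describe patients, visits and providers, and the article ties the final list to person-level balance. A clinic's prior performance is not among them.
- The secondary time points (6, 12 and 18 months) all follow activation, so differences between them cannot take out a gap that was there beforehand.

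A volunteer effect could therefore be read as a randomized effect on both primary outcomes.

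**Working it through.** **Inputs from the protocol article.** Randomization and Recruitment: 30 v 30 randomized, 6 v 30 analysed. Quantitative Analyses: intraclass correlation (ICC) 0.01 to 0.05; blood pressure 343 patients per clinic, 60% controlled; HbA1c 214 per clinic, 34% controlled; two-sided α 0.05. The agreement rate and the gap between agreers and refusers are not given, so they are assumptions here.

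**1. The protocol's own figures.** It states at least 80% power for differences of 9 to 17 points (blood pressure) and 10 to 18 points (HbA1c). Design effect = 1 + (m − 1)·ICC. For blood pressure this is 1 + 342 × 0.01 = 4.42 and 1 + 342 × 0.05 = 18.1; for HbA1c, 3.13 and 11.65. A two-proportion calculation on effective sample sizes gives these detectable differences at 80% power for an increase from baseline:

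| Clinics | Blood pressure | HbA1c |
|---|---|---|
| 6 v 30 | 6.9 to 13.6 | 7.3 to 14.2 |
| 6 v 6 | 8.8 to 17.2 | 9.5 to 18.6 |

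The stated figures lie close to 6 v 6. For 6 v 30, power at the stated differences is 0.94 to 0.97, so the claim of at least 80% holds and is no error. Power does not address bias.

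**2. Bias of 6 v 30 when the tools have no effect.** Let a be the fraction of clinics that would agree and D the amount by which agreers' control rate exceeds refusers'. Take the refusers' rate as R.

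- The 6 clinics: R + D.
- The controls, a mixture: R + aD.
- Difference: (1 − a)D.

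| D | a = 0.2 | a = 0.4 | a = 0.6 | a = 0.8 |
|---|---|---|---|---|
| 5 | 4 | 3 | 2 | 1 |
| 10 | 8 | 6 | 4 | 2 |

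The bias is zero if D = 0. In a given trial it also vanishes if no contacted clinic declines. A negative D reverses the sign.

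**3. What a given bias can do.** Blood pressure, 6 v 30, nominal 5% test, bias treated as a fixed shift. Standard error = √[p₁(1 − p₁)/n₁ + 0.24/n₀]. With ICC 0.01, n₁ = 6 × 343/4.42 = 466 and n₀ = 30 × 343/4.42 = 2,328. A 3-point bias gives a standard error of 0.0246, a shift of 0.03/0.0246 = 1.22 standard errors and a rejection rate of 23%. With ICC 0.05 it is 9%. A 6-point bias gives 70% and 23%. More patients per clinic do not remove the bias.

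**4. How large the bias can be.** The between-clinic variance of blood pressure control is ICC × 0.6 × 0.4 = ICC × 0.24, a clinic SD of 4.9 points at ICC 0.01 and 11.0 at ICC 0.05. Willingness alone contributes a(1 − a)D² to that variance, so the bias cannot exceed √[(1 − a)/a] clinic SDs. At a = 0.4 the ceiling is 1.22 SD: 6.0 points at ICC 0.01 and 13.4 at ICC 0.05. The 6-point illustration is thus the extreme case at ICC 0.01 (0.24 × 0.10² = 0.0024, all of the between-clinic variance) and uses one fifth of that variance at ICC 0.05 (0.0024/0.012). The 3-point case (D = 5) uses 25% and 5%. At a = 0.8 the ceiling is 0.5 SD, or 2.4 and 5.5 points.

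**5. What the as-randomized contrast can show.** In 30 v 30, 6/30 = 20% of the intervention group is exposed. A 9-point effect in the exposed clinics becomes 9 × 0.2 = 1.8 points, and 17 becomes 3.4. If the true effect equals the stated differences, power is 0.24 and 0.22 for blood pressure and 0.27 and 0.24 for HbA1c. Keeping only contacted clinics, decliners included, gives 0.72 to 0.81 if 10 are contacted and 0.49 to 0.59 if 15 are.

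**6. Why the contacted set is only approximately randomized.** Contact stops at the sixth agreement, so the last clinic contacted always agrees. The expected share agreeing, E(6/N), is 0.44 when the true rate is 0.40. For D = 10 the remaining bias is (0.44 − 0.40) × 10 = 0.4 points, against 6 points for 6 v 30.

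**The case against.** The strongest reply has five parts.

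- **Contact is in random order.** Clinics never reached are set aside without regard to their characteristics. This stands, and it limits the point. A reader might infer that all 24 clinics outside the intervention arm were selected out, or that the trial certainly compares volunteers with everyone. The article does not support that: only contacted clinics that decline cause selection, and their number is not known in advance.
- **The design is called quasi-experimental, and the recruitment scheme is described openly.** This is partial disclosure. It does not undo the explicit statement, in the section that defines the arms, that randomization between them is kept.
- **Covariates are to be chosen by observed balance.** This foresees some imbalance, but at person level. It does not reach a clinic's prior performance.
- **Intent-to-treat is set against per-protocol use of the tools, so it may mean enrolled clinics regardless of tool use.** That is a fair reading of the contrast. It is still not analysis by randomized group, and the article does not qualify the term.
- **Details of adjustment and tabulation may sit in an analysis plan not shown.** True, and their absence is not the point. The point rests on the comparison and the two claims that the article does state.

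**Conclusion.** The point holds in a conditional form. As written, the primary comparison filters one arm by consent after randomization and leaves the other unfiltered. It keeps the protection of randomization only if no contacted clinic declines or willingness is unrelated to outcome, and the protocol secures neither. The statement that randomization between the arms is preserved, and the unqualified intent-to-treat label, are therefore wrong for 6 v 30.

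The size and direction of the bias cannot be determined from the article. The figures of 3 and 6 points assume an agreement rate of 0.4 and gaps of 5 and 10 points between agreers and refusers; 6 points is the ceiling at ICC 0.01. A reader might go further and infer that the result will be biased in favour of the tools, or by a known amount. Nothing in the article supports either.

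**What to change.** 1. Describe 6 v 30 as a comparison of participating with control clinics, and remove the randomization and intent-to-treat claims for it. Adjust it for each clinic's pre-activation value of the same quality measure, available from the shared EHR.
2. Beside it, report the 30 v 30 contrast by randomized group as a bias check. The membership agreement already allows research use of all clinics' EHR data. State that only 20% of the intervention group is exposed and that power is about 0.22 to 0.27 at the protocol's detectable differences, so a null result there is not evidence of no effect. Contacted clinics (agreeing and declining) v controls may be added as a more precise check, labelled approximately randomized because contact stops at the sixth agreement.
3. Report how many clinics were contacted and how many declined, with pre-activation quality measures for agreeing, declining and control clinics.

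The cost is revised wording, some further data extraction and a more modest causal claim for the main comparison. No new consent or recruitment is needed.

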#### Data

All quantitative data will be extracted from OCHIN’s Epic EHR; these data are centrally managed and quality checked [44-46]. Qualitative data for the intervention phase will be collected via semistructured interviews with diverse clinic staff who interface with the CDS tools during patient care (eg, providers, care managers, and medical assistants) and an EHR-embedded provider card study at each study site. The interviews will explore relevant clinical contexts, perceptions and use of social risk data and CDS tools in clinical encounters, and the impact of patient-reported social risk data on clinical decision-making, quality of care, and patient-provider interactions, including potential negative impacts of tool use. Card studies are short (<1 minute) surveys designed to obtain point-of-care data on clinical decision-making [47]. This card study, which will be embedded within the EHR and, therefore, the provider workflow, will be used to assess provider reactions to and actions taken based on patient-reported social risk data.

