#### Quantitative Analyses

We will describe the percentage of clinic encounters at which (1) the CDS tools appeared to users at the intervention clinics, (2) users reviewed tool suggestions, and (3) the suggested care plan adaptations were enacted.

The primary trial outcomes are changes in the two CQMs expected to be affected by social risk–informed care: blood pressure control and HbA_1c_ control. Each CQM’s denominator will be defined according to which patients are eligible for that measure at the time of a clinic visit (eg, patients with diabetes are in the HbA_1c_ measure denominator) per national CQM measurement specifications [41]. Two-level hierarchical linear models [48-50] will be used to assess the impact of CDS tools on these outcomes. As these outcomes are binary, the generalized form of the hierarchical linear model with a log link and binomial distribution will be used. Textbox 1 shows other potential covariates; this list will be finalized based on the extent to which person-level covariates were balanced between the final intervention and control arms and will be included in the first level of the model representing the person level. The second level of the model, the CHC level, will include arm as an independent variable (control vs intervention) and a random effect for the intercept (ie, intercept-as-outcomes model). Population-averaged marginal proportions and associated 95% CIs will be calculated by arm, along with the difference between those proportions (ie, the marginal effect) and the associated 95% CI that incorporates the random effects (ie, differences between CHCs) and any included covariates.

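### Neither the draw of the six intervention clinics nor the clinic level of the model uses each clinic's pre-activation control rate, so an avoidable loss of precision is accepted

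*Protocol article*

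**What the plan says.** Under Randomization and Recruitment the article expects about 60 eligible clinics. It continues: "Eligible clinics will be randomized 1:1 to 1 of 2 groups: potential intervention or control". Then "Clinics from the potential intervention group (n=30) will be recruited in random order until 6 agree to participate". The comparison is 6 against 30 clinics. No stratification, matching or constraint is mentioned at either step.

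The same section notes that "all OCHIN member CHCs agree that their EHR data may be used in research as part of their membership agreement", and the Data section adds: "All quantitative data will be extracted from OCHIN’s Epic EHR; these data are centrally managed and quality checked". Under Quantitative Analyses, the overall baseline control rates used for power (60% for blood pressure, 34% for HbA1c) are already taken from these data.

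On the model, Quantitative Analyses says: "The second level of the model, the CHC level, will include arm as an independent variable (control vs intervention"), together with a random intercept. The other covariates listed are mainly patient, visit and provider characteristics. They enter at the person level and are finalized after balance has been inspected. The secondary model adds time at 6, 12 and 18 months, with no period before activation. The primary outcomes are nevertheless described as changes in the two measures.

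**The concern.** The intervention arm rests on six clinic-level results. Clinics differ in their usual control rates, and a clinic with high control before activation will tend to have high control afterwards. If the six happen to start above or below the 30 controls, part of that gap carries into the follow-up comparison. The model as described has no clinic-level term that removes it.

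The information needed to remove it is within reach before the trial starts. Without it the estimate is noisier than it need be, and a reader who sees a visible baseline gap has grounds to doubt a single six-clinic result in either direction.

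**Working it through.** **Inputs from the article.** Clinics: 6 v 30. ICC: 0.01 to 0.05. Blood pressure: 60% control, 343 patients per clinic. HbA1c: 34% control, 214 patients per clinic. Stated detectable differences at 80% power and two-sided 0.05: 9-17 points and 10-18 points.

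**Assumed, not in the article.** Equal clinic sizes, and a clinic-level correlation r between true pre-activation and follow-up rates of 0.5 to 0.8.

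**1. The plan's own figure.** With effective n per arm = clusters × m / (1 + (m − 1) × ICC) and a two-proportion test, 6 v 30 clinics give 6.9-13.6 points (blood pressure) and 7.3-14.2 (HbA1c). The stated ranges are not reproduced. They match 6 v 6 clinics (8.8-17.2 and 9.5-18.6) to within about half a point. The printed power is therefore conservative for 6 v 30. An allowance for unequal clinic sizes could also explain the difference. Nothing below depends on this.

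**2. Baseline gap in true clinic rates.** SD = √[p(1 − p) × ICC × (1/6 + 1/30)], where 1/6 + 1/30 = 0.2.
- Blood pressure, ICC 0.01: √(0.24 × 0.01 × 0.2) = 2.2 points
- Blood pressure, ICC 0.05: √(0.24 × 0.05 × 0.2) = 4.9 points
- HbA1c: 2.1 and 4.7 points

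For observed rates, replace ICC by ICC + (1 − ICC)/m. Blood pressure then gives 2.5 and 5.0 points.

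| Blood pressure gap | ICC 0.01 (true / observed) | ICC 0.05 (true / observed) |
|---|---|---|
| above 3 points | 17% / 23% | 54% / 55% |
| above 5 points | 2% / 4% | 31% / 32% |
| above 10 points | about 0% | 4% / 5% |

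HbA1c is much the same: a gap above 5 points has a chance of 2-5% at ICC 0.01 and 29-31% at ICC 0.05.

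**3. What clinic baseline adjustment saves.** Let V be the variance of an observed clinic rate and v = p(1 − p) × ICC its true between-clinic part. Unadjusted, the SD of the null difference is √(0.2 V). Adjusted for the observed baseline rate it is √(0.2 × [V − (r v)²/V]).

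Blood pressure, ICC 0.05: v = 0.0120 and V = 0.24 × (0.05 + 0.95/343) = 0.01267.
- Unadjusted: √(0.2 × 0.01267) = 5.0 points
- r = 0.8: √(0.2 × [0.01267 − 0.0096²/0.01267]) = 3.3 points
- r = 0.5: √(0.2 × [0.01267 − 0.0060²/0.01267]) = 4.4 points

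Blood pressure, ICC 0.01: v = 0.0024 and V = 0.24 × (0.01 + 0.99/343) = 0.00309.
- Unadjusted: 2.5 points
- r = 0.8: 1.95 points
- r = 0.5: 2.3 points

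A simulation of 36 clinics in which the slope is estimated (20,000 runs per setting) gives 3.3 and 4.5 points at ICC 0.05, and 2.0 and 2.3 at ICC 0.01. Estimating the slope costs little. For HbA1c the simulated SD falls from 4.9 to 3.4 (r = 0.8) or 4.5 (r = 0.5) at ICC 0.05, and from 2.6 to 2.2 or 2.4 at ICC 0.01.

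**4. What stratifying saves.** With six bands of 10 clinics ranked on blood pressure control alone and one intervention clinic per band, the SD of the observed baseline gap falls from 5.0 to 1.4 points (ICC 0.05). The SD of the null follow-up difference falls from 5.0 to about 3.5 at r = 0.8, which is no better than the covariate. Stratifying only the 1:1 split leaves a baseline-gap SD of 4.2, because the analysed arm is the six that are contacted and agree. Six strata built jointly on blood pressure control, HbA1c control and size leave about a 16% chance of a blood pressure gap above 5 points and a follow-up SD of about 4.2.

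**The case against.** - **Silence in a condensed article.** The text never says that the split or the contact order is unrestricted, and the full protocol may specify strata. This stands, so the point is confined to what is described. The model's clinic-level content, by contrast, is stated and not merely left out.
- **Chance imbalance is already in the error term.** Between-clinic variation enters the random intercept, the confidence interval and the ICC-based power statement. This also stands. A reader might infer that the comparison is biased by the draw; the documents do not support that.
- **A large imbalance is not likely.** A reader might infer that it is. Gaps above 5 points are rare at ICC 0.01 and occur in about a third of draws at ICC 0.05. Gaps above 10 points stay at or below about 5%. The stated detectable differences are 9-17 points.
- **Person-level adjustment already helps.** It may remove some clinic differences that come from case mix. It does not stand in for a clinic's own earlier control rate, and its content is settled only after balance is seen.
- **Stratifying has a cost.** Each stratum would hold about five candidates. If 30% of clinics agree (assumed), a stratum is exhausted with probability 0.7⁵ = 17%, and at least one of six with probability 1 − 0.83⁶ = 67%. At 50% agreement the latter is 17%. This is why stratifying is offered only as an option.

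**Conclusion.** The point holds as a matter of precision and credibility. Neither the described draw nor the described models use clinic baseline control, which the central EHR can supply. That each clinic's rate can be obtained is an inference from the data arrangements, though a safe one. The resulting chance gap has an SD of about 2 to 5 points over the stated ICC range, and its effect on the estimate is largely avoidable if clinic rates are stable over time.

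For blood pressure at r = 0.8, adjustment cuts the variance of the null difference by about 57% at ICC 0.05 (1 − 0.00539/0.01267) and 39% at ICC 0.01 (1 − 0.00190/0.00309). At r = 0.5 the cuts are about 22% and 15%. The correlation and the equal clinic sizes are assumptions. Imbalance in clinic size cannot be worked out, because the article gives no spread of sizes.

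A reader might also infer that the randomization must be stratified. It need not be: one clinic-level covariate, with the draw as written, does as well as ideal stratification on a single outcome. Neither measure addresses the separate matter that the six are clinics willing to take part.

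**What to change.** In the primary model, prespecify as a level-2 covariate each clinic's pre-activation control rate for the outcome being analysed. Compute it over a fixed window before activation, in the same target population (patients with known social risks), for all intervention and control clinics. Name it in the plan, so that it does not depend on the balance seen afterwards.

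Optionally, before recruitment, stratify both the 1:1 split and the contact order on one baseline score, such as pre-activation control. State that if no clinic in a stratum agrees, the next one is taken from the adjacent stratum. Do not build the strata from several variables at once, since six strata cannot balance them all.

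The cost is one EHR query, one clinic-level degree of freedom out of 36 clinics and, if the draw is stratified, possibly contacting more clinics. The covariate can be added at any time before outcome data are examined; the stratification only before recruitment starts.
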